## Project 6: to assess links between EF and treatment seeking for addiction and healthcare utilization and costs

### Background

P1-P5 will address psychological and biological mechanisms underlying EF and their implications for functional outcomes in SUDs. However, they will not directly evaluate public health impacts and individual experiences with treatment seeking. To complement these mechanistic insights and link them to potential policy implications, Project 6 (P6) will assess the links between domains of EF, treatment seeking and healthcare utilization.

Among individuals with a SUD, EF can affect retention (199–201) and engagement in treatment as well as treatment outcomes (25, 202), including the ability to achieve and maintain abstinence (199–201, 203). Given that SUDs are strongly associated with health care utilization (27), it is also likely that EF, which impacts the success of SUD treatment, is a key factor affecting the extent of health care utilization. In particular, among those with EF deficits, a diminished ability to achieve abstinence or low-risk alcohol use may lead to a higher use of emergency services for the acute consequences associated with SUDs (204). This could result in increased health care costs (205), which is problematic when existing resources dedicated to emergency services are limited (205, 206). Furthermore, a diminished ability to achieve abstinence or low-risk substance use may also lead to a higher use of non-emergency health care services, including primary care visits and hospitalizations, due to acute and chronic health effects associated with substance use (207, 208).

Furthermore, previous research has shown that EF is a factor in engagement in SUD treatment, including more treatment episodes and longer durations of abstinence among those without EF deficits (203). EF deficits lead to worse recognition of problem use (209–211). Therefore, people with EF deficits are more likely to view their symptoms as temporary or not serious, and consequently do not seek treatment (26). These factors may also affect whether patients stay in treatment or remain abstinent after treatment. Accordingly, it is likely that EF deficits affect treatment seeking behaviors, experiences, and barriers among people with SUDs.

### Objectives

P6 has two objectives. The first is to qualitatively assess the potential impact of EF on treatment-seeking behaviors, experiences, and barriers, specifically among individuals with AUD. The second objective is to quantitatively assess the association of EF with health care utilization among individuals with SUD, and to estimate the costs of this utilization.

#### H1

EF deficits will negatively impact treatment seeking and the treatment process as expressed by participants in treatment for AUD.

#### H2

Emergency and non-emergency health care utilization and related costs will be higher among participants in treatment for SUD with more severe EF deficits than among those with less severe EF deficits.

### Methods and planned analyses

#### Objective 1 (qualitative component)

A semi-structured, one-on-one 90-minute interview with a subset of participants recruited from the pooled CDiA sample will be conducted by a research coordinator trained in qualitative methods including interviewing and analysis, shortly after their baseline data are collected. Given differences in treatment pathways and trajectories and their potential impacts on treatment experiences, this analysis will be limited to participants with AUD. Interview questions will be related to treatment-seeking behaviors and EF. Participants will be asked about their experiences seeking help for substance use, perceived facilitators and barriers to treatment, perceptions and expectations regarding treatment, past health care utilization, and questions related to how EF (e.g., memory, attention, impulsivity, etc.) may have played a potential role in their treatment-seeking behavior and experiences. The interview will include probes to encourage participants to reflect on reasons for seeking treatment, including experiences with and perceptions of stigma. Participants will be asked about their social identities (e.g., age, sex and gender, ethnicities, etc.) and their EF, and whether or to what extent these factors have impacted their decision to seek treatment or their ability to benefit from and remain engaged in treatment. Additionally, in the absence of stigma being explicitly discussed by participants, stigma-related responses will be coded at the time of data analysis to interpretively identify the latent impact and role that stigma may have played on participants’ willingness to seek treatment.

This study will undertake a thematic analysis of the data obtained, examining and identifying common themes that emerge related to the perceived impact of EF on treatment-seeking behaviors, experiences, and barriers across the sample. We expect that thematic data saturation will be met with a sample size of approximately 30 participants.

All interview transcripts will be manually reviewed by a member of the research team, and an initial codebook will be prepared based on preliminary analyses. All transcripts will be coded for the initial set of codebook themes using NVivo software. As we anticipate both inductive and deductive themes to emerge from the data, the codebook will be subject to further development and revision based on ongoing analyses and discussion of emergent themes among members of the research team. Data analysis will be finalized once we have met data saturation, and no new themes emerge. Final results will be informed by common themes that emerged and were expressed by multiple participants. To increase data analysis credibility, a secondary independent coder will code a sub-sample of transcripts using the coding framework to assess inter-coder reliability, and any discrepancies between codes or themes will be discussed.

Subsequent to the interview, participants will be asked to complete the Behavior Rating Inventory for Executive Functioning in Adults (BRIEF-A), a standardized validated assessment that captures self-reported perceptions of an individual’s EFs and self-regulation (212). The results of the BRIEF-A assessment tool will be used to better understand the participants’ executive functioning from their perspective, which will further inform our qualitative analysis.

#### Objective 2 (quantitative component)

A health systems evaluation will be conducted to assess the association between EF (as measured in P1) and health care utilization, as well as the costs of this utilization. For this analysis, the database constructed in P1 will be linked with data on health care utilization and the associated costs obtained from the Institute for Clinical Evaluative Sciences (ICES). ICES will provide data on the use of publicly funded health services in Ontario. Participant data will be linked through ICES to the Hospital Discharge Abstract Database (DAD), National Ambulatory Care Reporting System (NACRS), Continuing Care Reporting System (CCRS), Ontario Health Insurance Plan Claims Database (OHIP), and Ontario Drug Benefit Claims (ODB) database. Records-level ICES data linkages will be performed using each participant’s unique Ontario Health Insurance Program health card number; the resulting database will be stripped of all direct personal identifiers and each entry will be assigned a confidential code number. All data linkages will be performed by an ICES data analyst. A subanalysis will be performed stratifying by conditions fully attributable and those not fully attributable to SUD.

Analyses will focus on the occurrence of service utilization, stratified by the type of service (i.e., non-emergency services and emergency services). The occurrence of health care service use among the cohort (recurrent time-to-event data) will be analyzed using multiple models, including covariates across multi-disciplinary domains. These models will include the Andersen and Gill model (i.e., generalizes the Cox model), Prentice, Williams and Peterson (PWP) model, marginal means/rates model, and frailty model (i.e., random effects model) (213–216). The final model to be used will be chosen based upon which of the previously used models best describes the data and which model assumptions are upheld. Model assumptions include the occurrence of an event being dependent upon the prior number of events during the follow-up period (PWP), there being no time-dependent covariates (marginal means/rates model), and the occurrence of an event cannot be explained by observed covariates alone (frailty model). Each statistical model will include covariates for the domains of EF, demographics, substance use, and health service utilization prior to study participation.

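### Project 6 picks its H2 model by fit and assumption checks that cannot validly choose among the four candidates, and one of them (PWP) removes part of the EF effect that H2 asks about

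*Protocol article*

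**What the plan says.** H2 of Project 6 is directional and concerns the amount of care used: "Emergency and non-emergency health care utilization and related costs will be higher among participants in treatment for SUD with more severe EF deficits", compared with participants whose deficits are milder.

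The Objective 2 (quantitative component) section of the protocol article treats service use as recurrent time-to-event data, split into emergency and non-emergency services. It names four models: Andersen-Gill, Prentice-Williams-Peterson (PWP), marginal means/rates, and frailty. The selection rule begins: "The final model to be used will be chosen based upon which of the previously used models best describes the data". The criterion in full is "which of the previously used models best describes the data and which model assumptions are upheld". So the rule has two parts, fit and assumptions.

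The section then lists conditions:
- for PWP, "the occurrence of an event being dependent upon the prior number of events during the follow-up period (PWP";
- for marginal means/rates, that no covariate is time-dependent;
- for frailty, "the occurrence of an event cannot be explained by observed covariates alone (frailty model".

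No condition is listed for Andersen-Gill. No fit criterion, order of precedence, effect measure or variance estimator is given. Every model carries the same covariate groups: EF domains, demographics, substance use and earlier service use.

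**The concern.** This is a rule that the article fixes, so a fuller analysis plan that followed it would inherit the difficulty. The chosen model supplies the test and the effect size for H2.

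H2 asks whether people with worse EF use more care in total. Andersen-Gill and marginal means/rates address that directly. PWP compares people who have already had the same number of events during follow-up. If worse EF produces more events, the earlier events are part of its effect, and conditioning on them takes that part out. Whether PWP fits well has no bearing on whether its coefficient answers H2.

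At stake is the size of the EF-utilization association, which is the policy result of Project 6. It could change materially with a choice made after seeing the data, on grounds that do not separate the candidates.

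**Working it through.** **Inputs.** From the article: the target sample of 400, the one-year follow-up, the four models and the selection rule. Project 6 states no event rate, effect size, heterogeneity or alpha, so there is no figure of its own to reproduce. Assumed here: complete one-year follow-up as the utilization window; a mean of m = 1, 2 or 4 events per person-year; gamma heterogeneity with mean 1 and variance θ = 0, 0.5, 1 or 2; one standardized baseline EF covariate; rate ratio 1.0 or 1.3 per SD (ln 1.3 = 0.262); two-sided 0.05.

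**1. Heterogeneity imitates event dependence.** Under a gamma-mixed Poisson process with no true event dependence, take a person with k earlier events at cumulative mean u. The intensity is proportional to e^(βx)(1 + θk) / (1 + θu·e^(βx)). Comparing k = 1 with k = 0 at the same time, the ratio is 1 + θ, that is 1.5, 2 and 3 for θ = 0.5, 1 and 2. The PWP condition therefore looks satisfied when only the frailty condition is true. The Project 7 Background itself treats heterogeneity as the norm in SUD.

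**2. Share of the effect that PWP keeps.** Near β = 0, the slope of that log intensity in βx is 1/(1 + θu), whatever k is. Averaged over u from 0 to m, the share kept is ln(1 + θm)/(θm). For m = 2:
- θ = 0.5: ln 2 / 1 = 0.69
- θ = 1: ln 3 / 2 = 0.55
- θ = 2: ln 5 / 4 = 0.40

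**3. Simulation** (300 replicates per setting, N = 400, true value 0.262, m = 2; frailty approximated by a negative binomial model, PWP on the total-time scale):

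| θ | Andersen-Gill / marginal | Frailty | PWP | Share kept by PWP |
|---|---|---|---|---|
| 0.5 | 0.261 | 0.261 | 0.180 | 0.69 |
| 1 | 0.267 | 0.269 | 0.146 | 0.56 |
| 2 | 0.264 | 0.264 | 0.107 | 0.41 |

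This agrees with step 2. At θ = 0 PWP kept essentially the whole effect. At 1 event per year the shares were 0.80, 0.68 and 0.55; at 4 per year, 0.55, 0.41 and 0.29. On the gap-time scale PWP lost a little less: at m = 2 the coefficients were 0.188, 0.160 and 0.124, or 0.72, 0.61 and 0.47 of 0.262.

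**4. No common fit scale.** The PWP stratified partial likelihood exceeded that of Andersen-Gill in 100% of replicates, including those where Andersen-Gill was true, so the raw comparison carries no information. Marginal means/rates is an estimating-equation method without a full likelihood.

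**5. Error rates with no EF effect, m = 2, θ = 0.5 / 1 / 2.**
- Andersen-Gill with model-based SE: 0.14 / 0.27 / 0.37. The approximation 2(1 − Φ(1.96/√(1 + mθ))) gives 0.26 at θ = 1.
- Marginal with robust SE: 0.04 / 0.06 / 0.09.
- Any significant result among the analyses with valid SEs (robust Andersen-Gill/marginal, robust PWP, frailty): 0.05 / 0.09 / 0.12.

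The Monte Carlo SE is about 0.013 at a rate of 0.05. Over all 12 rate-by-heterogeneity settings the robust marginal analysis averaged about 0.06, and its coefficient was 0.257 to 0.267 for a true 0.262.

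**The case against.** Several objections have force.

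- **The rule includes assumptions as well as fit.** True, and the frailty condition is exactly unexplained heterogeneity. In a separate simulated check with only Andersen-Gill and gamma frailty as candidates (1 or 2 events, θ = 0.5 to 2, no EF effect), a likelihood-ratio test chose frailty in every run and the error rate after selection was 0.045 to 0.058. That check left PWP out, however, and step 1 shows that the PWP condition would look satisfied in the same data. No order of precedence settles which should win.
- **A reader might infer that the four models estimate four different quantities.** They do not here. Andersen-Gill and marginal means/rates share a point estimate, and gamma frailty gave the same log rate ratio. Only PWP departs.
- **A reader might infer that the selection rule inflates false positives several-fold.** The documents do not support this. The large error rates need Andersen-Gill kept with model-based SE, and the article does not state the variance estimator.
- **A reader might infer that the EF effect will be halved.** Nothing ranks PWP first, and no probability of its being chosen can be given. At 2 events per year, a loss of half needs θ above 1. Adjustment for earlier service use, which the article requires, would reduce residual heterogeneity.
- **PWP can be the right model for another question.** With true event dependence (hazard × 1.3 per earlier event, no heterogeneity, baseline rate 1 per year), PWP returned 0.265 and the marginal model 0.327. Both are legitimate answers, but to different questions, so the target has to be named first.
- **All four models are to be fitted and could be shown side by side.** They could, but the article still commits to one final model.

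**Conclusion.** The concern holds in a limited form. The model for H2 is to be chosen after the data are seen, by a rule with no workable criterion across the candidates and with two conditions that heterogeneity makes hard to separate. If the rule leads to PWP, the reported EF coefficient answers a history-conditional question instead of H2's question about total use. Under the assumed 2 events per year, residual heterogeneity variance 0.5 to 2 and no true event dependence, it would be roughly 70% down to 40% of the marginal effect. The loss is smaller with less residual heterogeneity, and there is none when residual heterogeneity is absent.

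Error inflation is a secondary and conditional matter. It is several-fold only if Andersen-Gill is retained with model-based SE under such heterogeneity. With valid SEs, even taking any significant result gave about 0.05 to 0.12 across the settings.

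All sizes rest on assumed rates and heterogeneity with one covariate, before the planned adjustment. The logical defect in the rule does not depend on them.

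**What to change.** Delete the best-fit selection rule from the Objective 2 (quantitative component) section. Pre-specify as primary for H2 the marginal means/rates model with robust variance clustered on participant, fitted separately for emergency and non-emergency use and reported as a rate ratio per SD of EF. Report PWP and frailty as labelled sensitivity analyses, and state that the PWP coefficient is conditional on earlier events in follow-up and is not an estimate of the effect on total use.

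The cost is wording only: no new data, visits or participants. The statistical price is a slight loss of efficiency if a frailty model were exactly right.

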## Project 7: to identify subtypes of individuals seeking addiction treatment using cross-disciplinary data types from all projects to and map the biopsychosocial all-cause drivers of cognitive dysfunction in adult outpatients seeking treatment for SUD

### Background

P1-P6 will address targeted hypothesis-driven questions related to EF deficits and health outcomes in SUDs. To complement these hypothesis-driven efforts, Project 7 (P7) will integrate data types collected across all other projects to identify novel data-driven participant profiles and evaluate their utility in predicting outcomes over time.

In SUDs, heterogeneity is the rule rather than the exception (217). This heterogeneity is largely driven by extremely high rates of comorbid psychiatric conditions (218–220) and compounded challenges in the diagnostic process, as emergent cognitive syndromes may be temporary, drug induced, or chronic (221, 222). Even when considering the same SUD, symptoms and prognoses vary wildly between patients due to complex combinations of life experience (223), biology (224), and socio-demographic factors (225, 226). Given this heterogeneity, it is likely that there exist subpopulations, or subtypes (227–229), of individuals with similar diagnostic classifications but different underlying disease mechanisms and degrees of cognitive impairment. Due to these mechanistic differences, interventions aimed at improving deficits in EF (230) would not be expected to work equally well in different subtypes, meaning their identification is a priority for future applications of precision medicine in SUDs.

Attempts to define subgroups within and across diagnoses with relatively homogeneous symptom profiles and outcomes have met with limited success; for example, a five-biotype model of alcohol dependence has been proposed using latent class modeling of family history, age at onset, DSM-IV criteria, and data on comorbid illnesses (231). Others have proposed four- and two-group subtyping schemes based on psychiatric co-morbidity, family history, psychopathy, temperament, and other clinical health measures (232). Despite the strong links between symptom dimensions and executive dysfunction (see P1), subtypes have not been formally evaluated for differences in domains of inhibition, set shifting, or working memory updating, leaving a major gap in the field. To their detriment, most efforts have focused on relatively few domains of interest, not examined changes in cognitive performance (specifically EF) over time, and yielded varying, unstable results. Therefore, it is important to approach the problem from a data-inclusive perspective (233). Using insights from unimodal investigations, such as those proposed in the preceding CDiA projects, it is also possible to assemble optimal parsimonious predictive models at the individual level which could aid in screening efforts and clinical decision making.

### Objectives

Within Project 7 (P7), we propose to integrate data collected from each of the proceeding projects – including use of insights from animal experiments in Project 5 – to (1) perform multi-modal subtyping on SUD individuals, (2) evaluate subtypes against known biological risk profiles for cognitive dysfunction and psychiatric illness (such as exploring polygenic risk scores) and other longitudinal outcomes (e.g. TMS treatment outcome, specified in P4), and (3) use machine learning approaches to optimize predictors of cognitive dysfunction over time and to understand the structure of modifiable risk and resilience factors that may present opportunities for intervention. Within this broader framework, P7 will test the following specific hypotheses:

#### H1

Multi-modal unsupervised and semi-supervised clustering of SUD patients at baseline will reveal transdiagnostic subtypes of SUD with unique risk factor profiles and levels of EF.

#### H2

Subtypes from Aim 1 will be predictive of changes in EF over one year of follow-up and individuals with evidence for subgroup transition will experience different treatment response rates.

#### H3

Multivariate predictive models of changes in EF over time, incorporating the available multi-modal feature space of CDiA, will offer better performance than models based on individual modalities.

### Methods and planned analyses

#### Cross-sectional data-driven subtyping

This will involve using subject clustering algorithms to identify relatively homogeneous subgroups of patients. Primary measurements from each of P1-6 will be used as input for clustering (see **Table 4** for domain definitions). The similarity network fusion (SNF) method will then be used to combine more fine-detailed, high-dimensional input variables across multiple modalities. To address the key overarching theme of this proposal, subgroups based on EF domains (including and excluding other measures, as in P1 objectives) will be of particular interest, and will be tested for distributional differences in primary prognostic outcomes of functional recovery and sustained health. The semi-supervised association-boosted SNF (abSNF) method will be used to identify subgroups with most significance to EF performance at baseline. Internal validation of group membership will be performed using bootstrap procedures. Socio-demographic, educational, and life experiential characteristics of each subgroup will be described and placed within the context of existing cross-sectional work.

**Table 4 T4:** Summary of assessment domains and measurements across study projects.

Project	Domain (instrument/source)	Measures
1	Clinical (DART, suicidal ideation) + Substance use (TFLB, AUDIT, DUDIT, SDS)	Psychiatric diagnoses, comorbidity, suicidal ideation, childhood adversity, medication, treatment engagement
		Recent and lifetime history of (poly)substance use
		Age of onset, average yearly use, heaviest period of use
	Cognition (CNS-VS, executive function tasks, other behavioral tasks)	Global cognitive function
		Executive function (Inhibition, updating, set shifting) deficits and biases
		Risk and reward behavior
	Functional impairment and quality of life (WHOQOL-BREF, WHODAS)	Physical, psychological, social, and environmental
		Cognition, mobility, self-care, getting along, life activities, and participation
2	Neuroimaging (3T MRI)	Task-based and resting state fMRI
		T1-weighted structural MRI
		Neuromelanin-sensitive MRI of SN/VTA and LC
		Diffusion MRI
3	Genomics	Assay-based genome-wide genotypes
		Assay-based genome-wide methylation profiles
	Plasma biomarkers	Inflammasome proteins (NF-KB, ERK, and p38MAPK, NALP3)
		Pro-inflammatory cytokines (IL-1β, IL-18, and ProCaspase-1)
4	Intervention (4 week TMS) clinical outcomes	Suicidal ideation (SSI)
		Depressive symptoms (HRSD-17)
	Intervention electrophysiological outcomes	Electroencephalogram (EEG)-derived GABA receptor mediated inhibition

This table does not list every measurement from every project and core, though it provides an overview of the types of measurements belonging to each general domain analyzed in P7. P5 is absent, as measures taken from rodent models will not be directly included as features in human sample statistical modeling.

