#### Supervised machine learning for prognostication

We will apply machine learning methods on features identified by each project across domains to build optimally predictive models of: (1) EF, (2) social function, (3) suicidality and self-harm, and (4) healthcare system burden (234). Modelling will proceed iteratively, using processes developed by our group (235–237).

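### Project 7 clusters on baseline EF, then counts EF level (H1) and one-year EF change (H2) as evidence for the subtypes

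*Protocol article*

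**What the plan says.** All places are in the protocol article, Project 7 unless stated.

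- **Inputs.** Under Cross-sectional data-driven subtyping: "Primary measurements from each of P1-6 will be used as input for clustering". Table 4, cited there for the domains, includes under Project 1 "Executive function (Inhibition, updating, set shifting) deficits and biases".
- **EF-based subgroups.** In the same section, "subgroups based on EF domains (including and excluding other measures, as in P1 objectives) will be of particular interest". The option adds or drops the other measures; EF stays in either way.
- **abSNF.** This method "will be used to identify subgroups with most significance to EF performance at baseline".
- **H1.** Clustering at baseline "will reveal transdiagnostic subtypes of SUD with unique risk factor profiles and levels of EF".
- **H2, first clause.** "Subtypes from Aim 1 will be predictive of changes in EF over one year of follow-up".
- **Stated checks.** Group membership is bootstrapped, and clustering is repeated independently at several time points. EF-domain subgroups are also compared on functional recovery and sustained health.

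The article does not say how EF change will be modelled. It ties neither H1 nor H2 to a clustering solution formed without EF.

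**The concern.** The variable that forms the groups is also the variable used to show that the groups are meaningful. Cutting one homogeneous population by EF gives groups that differ in EF, whether or not subtypes exist. The low-EF group also contains more people whose baseline score was low by measurement error, so its average moves up on retest and the high-EF group's moves down. A raw comparison of change then looks like prediction.

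At stake is whether H1 (its EF-level clause) and H2 (its first clause) can fail. If they cannot, the program could report EF subtypes with differing EF trajectories from data that contain neither.

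**Working it through.** Project 7 gives no sample size, alpha or power, so there is no figure to reproduce. The check is a null simulation.

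**From the article:** cohort 400 (Project 1, Design and participants); about 200 expected with MRI (Project 2, Participants); three EF domains; EF measured at baseline and one year.

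**Assumed, because the article gives no value:** retest reliability 0.5-0.9, correlation of 0.3 between EF domains, 2-4 clusters, and the number of non-EF inputs.

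**Null model:** one Gaussian population, no subtypes, no true change. Follow-up EF is the same true score plus fresh error, and non-EF inputs are unrelated to EF. Tests at 0.05: ANOVA of baseline EF by cluster; ANOVA of EF change by cluster; ANCOVA of follow-up EF by cluster with baseline EF as covariate. There were 300 runs per k-means cell, 120 per SNF cell at n=200 and 50 at n=400.

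**Mechanism.** Take one standardised EF score b at baseline, f at follow-up and retest correlation ρ, with groups formed on b alone. Then E(f − b | b) = −(1 − ρ)b. Two clusters a distance D apart at baseline show a spurious gap of (1 − ρ)D in change: 0.5D, 0.3D and 0.1D at ρ = 0.5, 0.7 and 0.9. With b as covariate, E(f | b) = ρb, which leaves nothing for cluster to explain.

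**EF-only inputs, three clusters.** Baseline EF differed in 100% of runs in every cell. For EF change:

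| Reliability | Unadjusted, n=400 | Unadjusted, n=200 | Spurious gap in change, n=400 (SD) | ANCOVA, n=400 |
|---|---|---|---|---|
| 0.5 | 100% | 98% | 0.71 | 4% |
| 0.7 | 100% | 92% | 0.39 | 5% |
| 0.8 | 97% | 78% | 0.26 | 5% |
| 0.9 | 71% | 41% | 0.13 | 5% |

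Two or four clusters at n=400 gave 71-100% unadjusted.

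**Other solutions, n=400, three clusters** (ranges over reliability 0.5, 0.7 and 0.9; abSNF at 0.5 and 0.7 only):

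| Clustering | Baseline EF differs | Unadjusted change differs | ANCOVA |
|---|---|---|---|
| k-means, EF + 10 unrelated inputs | 100% | 67-99% | 5-6% |
| k-means, EF + 30 | 96-100% | 46-81% | 5-6% |
| k-means, EF + 100 | 73-92% | 14-35% | 4-6% |
| Unsupervised SNF, five modalities | 88-100% | 18-60% | 4-8% |
| abSNF, five modalities | 100% | 98% | 4% |
| k-means, EF left out | 4-7% | 3-5% | 2-6% |

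At n=200, unsupervised SNF gave 87-93% for baseline EF and 13-48% for change. abSNF gave 100% for baseline EF, and 98%, 82% and 32% for change at reliability 0.5, 0.7 and 0.9.

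A second k-means simulation at n=400 gave 76-100% for change with EF-only inputs. With 17 to 97 unrelated inputs added it gave 70-100% for baseline EF and 10-90% for change. Adjustment for baseline EF brought change to 3-7%, and leaving EF out of the inputs gave 2-7%.

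**Simulation error around 5%:** √(0.05 × 0.95/300) = 1.3 percentage points with 300 runs, and √(0.05 × 0.95/50) = 3.1 points with 50. The adjusted and EF-free rates are therefore compatible with 5%.

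**The case against.** **The change model is unstated.** The article specifies no unadjusted change-score test, and an analysis plan normally settles this. That stands, so the H2 point is conditional. It does not rescue H1, whose EF-level clause depends only on the stated inputs, the stated abSNF target and the stated hypothesis.

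**The stated subgroup comparison is on functional recovery, not EF.** That is the sounder test, and EF-only clusters keep functional scores out of the inputs. It should stay. But H1 and H2 are worded in terms of EF.

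**Bootstrap and re-clustering would expose unreal clusters.** In part. Under a no-subtype null, mean bootstrap agreement (adjusted Rand index) was 0.30 with 6 inputs and 0.14 with 20, but about 0.6 when EF scores correlated 0.3. The article gives no threshold, and a reproducible cut through EF is just as circular.

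**Clustering within single data types gives EF-free solutions.** True, imaging alone for example, but the article does not assign the EF tests to them.

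**Stronger readings a reader might infer, which the article does not support:**
- *H1 as a whole is true by construction.* Only the EF-level clause is, and only for EF-based and abSNF subtypes. Unsupervised multi-modal clustering makes it likely, not certain, and nothing guarantees the transdiagnostic clause.
- *Project 4 post-treatment outcomes are clustering inputs.* Table 4 lists Project 4 outcome domains, and the Objectives name "other longitudinal outcomes (e.g. TMS treatment outcome, specified in P4" as something to evaluate subtypes against. But H1 clusters at baseline, and Table 4 is cited only to define domains. The depression scale and TMS-EEG measures also have pre-treatment values, and Project 4 enrols 40 of the 400.
- *H3 suffers from feature-selection leakage.* The article says "We will apply machine learning methods on features identified by each project across domains to build optimally predictive models" and refers to the group's published processes. It states no selection rule or validation scheme that could be faulted.

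**Conclusion.** The concern holds in limited form. For EF-based and abSNF subtypes, a difference in baseline EF is built in and is no evidence for H1. For unsupervised multi-modal subtypes it appears in about 70-100% of null runs and so carries little weight.

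H2's first clause is at risk only if change is tested without baseline EF. In that case the false-positive rate at n=400 is about 70-100% for EF-only subtypes. For multi-modal subtypes it is about 10-90%, falling as non-EF inputs are added and reaching 99% with only ten of them. The nominal rate is 5%. H2's second clause, on subgroup transition and treatment response, is a separate question that these results do not address.

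The sizes rest on the assumed reliability of 0.5-0.9, on non-EF inputs unrelated to EF, and on simple versions of the clustering methods. The direction does not depend on them. The simulations do not suggest that real subtypes are absent; they show that these two criteria cannot tell.

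**What to change.** 1. Test EF level (H1) and EF change (H2, first clause) on a clustering solution that leaves EF out of the inputs.
2. Report EF-based and abSNF subtypes as descriptive with respect to EF, and keep their comparison on functional recovery.
3. In H2, model 12-month EF with baseline EF as a covariate.
4. For clarity, add that only pre-treatment Project 4 values enter baseline clustering.

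In the simulations, step 1 brought the false-positive rates to 4-7% for EF level and 3-5% for change, and step 3 brought change to 2-8%. No new data are needed, only analysis wording and computing time. The drawback is that EF-free subtypes may show weaker separation on EF.
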